#### Telehealth Platform

The My Health, My Life, My Way telehealth platform will be used by participants throughout the duration of the study. On the platform, participants will be able to access educational multimedia content (videos and articles), track and log medication use, create and track health-related goals, and access food- and nutrition-related information. In addition, participants will be able to view upcoming health coaching calls and contact the health coaching team using the messaging feature of the platform.

### Participant Study Activities

#### Gamification Component

All participants, regardless of gamification variation, will be able to obtain points and badges on the platform. Participants can check their points status at any time during the study by logging in to the platform to view an itemized list for all badges and points. In addition, participants will be provided email notifications for all gamification updates. All activities, such as viewing and reading educational content and logging in to the platform, will automatically be updated on the platform. Health coaches will encourage participants to engage on the platform regularly. Those not receiving scheduled coaching calls who exercise the on-demand coaching option will be encouraged by a health coach to use the platform regularly.

#### Health Coaching Component

Those receiving scheduled health coaching calls will be able to view upcoming calls on the platform. In addition, email and SMS text messaging notifications will be provided to remind participants of all scheduled coaching calls. Scheduled coaching calls will occur once per week and are expected to last up to 60 minutes. Those who will not receive scheduled coaching calls will still have access to the study platform. Within the platform, participants will be able to contact health coaching staff if they desire on-demand coaching. With this on-demand coaching function, participants can discuss any questions regarding educational content on the platform.

### Exit Interviews

After the study duration, up to 30 participants from the My Health, My Life, My Way program will be contacted for a follow-up interview to obtain their experiences and feedback with the My Health, My Life, My Way telehealth platform. These interviews will be conducted on the web.

### Data Collection Methods

#### Outcome Measures

Primary and secondary outcome measures will be assessed at baseline, 3 months, and 6 months (after the intervention). The primary clinical outcome measure is health-related quality of life; the secondary outcome measures are described in Table 2 along with the primary outcome measure.

##### Health-Related Quality of Life

The primary outcome measure is health-related quality of life. This will be measured by using the 36-item Short Form Health Survey, enabled version (SF-36E). More specifically, the physical functioning section of the SF-36E has been modified, which uses disability-friendly inclusive language for individuals with mobility impairments [4].

All other measures, including demographic data and secondary outcome measures, will be retrieved and automatically stored through electronic surveys delivered by REDCap. All self-reported items within the questionnaires will be mandatory to prevent missing data. The questionnaire packet will be delivered electronically to the participants during the study.

##### PA Measurements

To measure PA, participants will complete the Godin Leisure-Time Exercise Questionnaire. This 3-item questionnaire asks questions related to strenuous, moderate, and light exercises performed during the past 7 days [32]. In addition, activity counts and time spent in PA will be collected from the participant’s Fitbit device.

##### Self-efficacy for Managing Symptoms

Participants will complete the Patient-Reported Outcomes Measurement Information System (PROMIS) Item Bank v1.0–Self-Efficacy for Managing Chronic Conditions–Managing Symptoms–Short Form 4a, which is a 4-item survey that assesses confidence in managing symptoms associated with their chronic health condition [33].

##### Self-efficacy for Managing Daily Activities

To assess confidence in handling daily activities, participants will complete the 4-item PROMIS Item Bank v1.0–Self-Efficacy for Chronic Conditions–Managing Daily Activities–Short Form 4a [33].

##### Self-efficacy for Managing Sleep Disturbances

Participants will complete the PROMIS Item Bank v1.0–Sleep Disturbance–Short Form 4a, which is a 4-item survey that evaluates sleeping habits during the previous 7 days [33].

##### Psychosocial Illness

To assess self-efficacy for managing psychosocial illness, participants will complete the PROMIS Psychosocial Illness Impact-Positive–Short Form 8a [33]. This questionnaire includes 8 items that evaluate psychosocial illness before and after an illness.

##### Self-efficacy for Managing Emotions

To assess the ability to manage emotions, participants will complete the PROMIS Item Bank v1.0–Self-Efficacy for Managing Chronic Conditions–Managing Emotions–Short Form 4a [33]. This survey includes 4 items regarding the ability to manage emotions while experiencing chronic health conditions.

##### Self-efficacy for Managing Social Interactions

Participants will complete the PROMIS Item Bank v1.0–Self-Efficacy for Managing Chronic Conditions–Managing Social Interactions–Short Form 4a [33]. This 4-item survey will assess an individual’s perceived ability to engage in meaningful social interactions.

##### Emotional Distress

To assess self-efficacy for managing depression, participants will complete the PROMIS Item Bank v1.0–Emotional Distress-Depression–Short Form 4a [33]. This survey includes 4 questions about participants’ emotions within the past week.

##### Self-efficacy for Managing Medications and Treatment

To assess confidence in managing medications and treatment, participants will complete the 4-item PROMIS Item Bank v1.0–Self-Efficacy for Managing Chronic Conditions–Managing Medications and Treatment–Short Form 4a [33].

##### Self-efficacy for Managing Sleep-Related Impairments

Participants will complete the PROMIS Short Form v1.0–Sleep-Related Impairment 4a to evaluate overall sleep quality during the previous 7-day period [33].

##### Dietary Intake

Participants will complete the Short Healthy Eating Index (sHEI) survey, which is a 23-item survey that evaluates nutritional habits, such as fruit and vegetable consumption, water intake, and sugar consumption [34].

##### Medication Adherence

To measure medication adherence, participants will complete the Medication Adherence Rating Scale (MARS). The MARS is a general, 10-item binary questionnaire that asks questions related to regularly taking medication [35]. Medication adherence will also be measured using the Beliefs About Medication Questionnaire (BMQ). The BMQ is an 18-item questionnaire that includes Likert-style questions regarding personal beliefs about how medications influence daily living [36].

##### Telehealth Dashboard Usability

To measure the usability of the telehealth dashboard, participants will complete the System Usability Scale (SUS) and the Health Information Technology Usability Evaluation Scale (Health-ITUES). These Likert scales include items asking about the dashboard’s effectiveness (ability to complete tasks), efficiency (level of dashboard use), and satisfaction (subjective reactions to the dashboard) [37,38].

##### Medication and Dosage

Participants will be asked to provide current medications and dosages throughout the study duration to control medication data during the statistical analysis.

### Feasibility Measures

This study will obtain measures related to the feasibility and acceptability of the My Health, My Life, My Way intervention on self-management for individuals with disabilities who also experience chronic conditions. Measures will include process, resource, scientific, and management feasibility outcomes. All elements of intervention delivery will be collected, including but not limited to adherence, retention, attrition, coach and participant communication needs, staff preparation, and adverse events. Obtaining these measures will inform future considerations in the delivery of a web-based self-management program for people with disabilities.

### Data Management

All data collected will be entered directly into REDCap and stored. Participants will be assigned a participant number upon enrollment in the study. Only approved study personnel will have access to the REDCap program, where data will be stored. Data checking will involve confirming that surveys, questionnaires, and health coaching calls are completed.

### Statistical Methods

All statistical analyses will be conducted in an intent-to-treat manner at the individual level taking into account the correlated nature of data (multiple time points for every participant). Statistical significance will be evaluated at a type I error rate of 5%. Quality control will include descriptive and graphical approaches to summarize baseline characteristics of all key variables. With respect to data, we will begin by systematically cleaning and verifying all collected data, as well as examining ranges, missing values, and provenance. The significance tests conducted for the primary outcome are all specified a priori and modest in number. Consistent with published guidelines for statistical reporting, exact *P* values (rather than, eg, “*P*<.05” or “NS” [not significant]) will be reported [39]. This allows readers who may have their own opinions about multiple testing corrections, configurations of a family of hypotheses, and costs of type I errors to set the significance level to know the raw, uncorrected result and make their own judgments about statistical significance [40,41]. As Saville [42] noted, in multiple comparison issues, there is no right answer, and each investigator must ultimately “cut the Gordian knot” themselves. To evaluate the potential systematic variation among the study arms, key variables such as age, race, sex, disability type, and physical function at baseline will be examined and compared for relationships with study arms. If a potential confounder is found to differ meaningfully among the groups and if we find that the inclusion of the covariate improves the corrected Akaike information criterion (AIC), it will be included as a covariate in our analyses. We will estimate and test the effects of the 4 individual intervention components by means of a full factorial experiment. First, we will fit a linear mixed model to account for correlated data, to check whether each factor has a significant effect on outcome change across the time points (baseline and 6 months). For each of the 2 components, we will determine whether there is a difference in change across time using baseline as the reference cell (ie, 6 months vs baseline). This would be considered the main effect of each component on the pre-post difference. However, statistically, these effects will be modeled as component-by-time interactions, with the 6-month outcome as the primary end point. We will also include interactions among the components (eg, factor 1 × factor 2 × time interaction). In terms of multiple testing, given that this is a pilot project (ie, an exploratory and not confirmatory trial), we will estimate the false discovery rate and false discovery proportion based on the *P* values for all outcomes.

Our 3-pronged approach involves minimizing missing data, leveraging the maximum likelihood–based approach or the multiple imputation approach under the assumptions of ignorability (ie, missing-at-random [MAR] assumption), and conducting multiple sensitivity analyses assuming MAR as well as missing not at random [43,44]. Analytically, our choice of mixed models to account for the repeated nature of the data will allow us to handle missing data for the primary and secondary outcomes under the assumptions of MAR. The MAR mechanism is ignorable when mild regularity conditions are satisfied. Such inferences can proceed by analyzing the observed data only, without explicitly addressing a form of the MAR mechanism. Missing data in other independent variables (mediators or other covariates) will be handled through the expectation-maximization algorithm coupled with bootstrapping for SEs, which will give maximum likelihood–based imputation under the MAR assumption [43].

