### Sample Size

We will use a 2 × 2 factorial design for this MOST trial (detailed in the Intervention Design subsection). Our sample size and power calculations for the primary outcome (health-related quality of life) assume an overall 2-sided type I error rate of 5%, 80% power, and an analysis of covariance–based approach with 2 independent dichotomous factors (ie, each factor has 2 levels). We will assume an attrition rate of 20%, with 160 (80%) participants completing the study (referred to as completers) from 200 participants enrolled. Under these assumptions, we will have 80% power to detect at least a minimally detectable difference (Cohen *d*) of 0.36 for the main effect or 0.18 in terms of the standardized regression coefficient. In these calculations, we assume a conservative correlation of 0.6 between the baseline covariate and outcome, which is similar to that in a previous study by Froehlich-Grobe et al [4]. In addition, 12 participants will be enrolled for pilot-testing the My Health, My Life, My Way program [28].

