### Overview of the Intervention

#### Orientation Call

After the welcome call and randomization, a study health coach will be notified through REDCap that a participant has been randomized to one of the study arms and will conduct an orientation call with the participant. The purpose of this call by the health coach is to introduce themselves to the participants as their primary health coach and to schedule the first weekly coaching call. For those not receiving scheduled coaching calls, the health coach will inform participants that they can contact the coaching staff during the study to ask questions related to the educational content provided on the platform.

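### The model and the detectable difference of 0.36 make no allowance for coach clustering; if coaches differ mainly in the scheduled-call level, both are too favourable for the coaching effect

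*Protocol article*

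**What the plan says.** Protocol article, Statistical Methods: the analysis is run "at the individual level taking into account the correlated nature of data (multiple time points for every participant". The paragraph on missing data in the same section again ties the choice of mixed models to the repeated measurements. No coach effect is mentioned.

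Sample Size: the calculation assumes an "overall 2-sided type I error rate of 5%, 80% power" and an analysis-of-covariance "approach with 2 independent dichotomous factors". On completion it says "We will assume an attrition rate of 20%, with 160 (80%) participants completing the study". The detectable difference is "0.36 for the main effect or 0.18 in terms of the standardized regression coefficient", with a baseline-outcome correlation of 0.6. No cluster term or design effect is mentioned.

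Orientation Call: after randomization a coach calls to "introduce themselves to the participants as their primary health coach".

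Health Coaching Component: "Scheduled coaching calls will occur once per week and are expected to last up to 60 minutes". The study lasts 24 weeks (Intervention Design). Participants without scheduled calls have on-demand contact only (Coaching Calls; Participant Timelines and Intervention Duration).

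The article does not give the number of coaches, how they are assigned across arms, or an ICC for coach.

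**The concern.** When an intervention is delivered by a small number of people, the outcomes of participants who share a provider can be correlated. Here the exposure is unequal by design: one level of the coaching factor has weekly calls of up to an hour, the other has occasional contact at the participant's request. Coach-to-coach variation could therefore load mainly on one side of the coaching contrast, which is a partially nested design. A model that handles only repeated measures within a person would then understate the uncertainty of that contrast.

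Scheduled calls are one of the two components the trial is meant to judge. The Discussion says that, if they prove more effective than on-demand contact, future programs should consider putting more resources into coaching. An overconfident coaching effect would feed directly into that decision. Reporting exact P values and estimating false discovery rates does not help, because both start from the same P values.

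**Working it through.** **Inputs from the documents.** Two-sided alpha 0.05 and 80% power; 160 completers, so 80 per level of each factor under 1:1:1:1 allocation (Allocation); baseline-outcome correlation 0.6, so residual variance 1 − 0.6² = 0.64 and residual SD 0.8.

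**Step 1: reproduce 0.36 with independent participants.**

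- SE = 0.8 × √(1/80 + 1/80) = 0.1265.
- Detectable difference = (1.96 + 0.84) × 0.1265 = 0.354 (normal) or 0.357 (t distribution). The standardized coefficient is half of this, 0.177 to 0.178.
- Power at 0.36 is 81.2% (normal) or 80.7% (t). Attrition agrees: 160 / 0.8 = 200.

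The stated figure is confirmed, and it contains no allowance for coach clustering.

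**Step 2: add coach variance in the scheduled level only.** Assumed, not in the documents: k coaches with equal caseloads of m = 80/k scheduled-call completers, and an ICC ρ on the baseline-adjusted scale.

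- Design effect DE = 1 + (m − 1)ρ.
- True SE = 0.8 × √(DE/80 + 1/80).
- Variance inflation = (DE + 1)/2.
- Type I error of the unadjusted test = 2 × [1 − Φ(1.96/√inflation)].
- Detectable difference = 2.80 × true SE; power at 0.36 = Φ(0.36/true SE − 1.96). Both are for a test that uses the true SE.

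| Coaches | ICC | DE | SE | Type I error | Power at 0.36 | Detectable difference |
|---|---|---|---|---|---|---|
| any | 0 | 1.00 | 0.126 | 5.0% | 81% | 0.354 |
| 10 | 0.01 | 1.07 | 0.129 | 5.4% | 80% | 0.361 |
| 8 | 0.01 | 1.09 | 0.129 | 5.5% | 80% | 0.362 |
| 4 | 0.01 | 1.19 | 0.132 | 6.1% | 78% | 0.371 |
| 8 | 0.05 | 1.45 | 0.140 | 7.7% | 73% | 0.392 |
| 4 | 0.05 | 1.95 | 0.154 | 10.7% | 65% | 0.430 |

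Worked case, 4 coaches and ICC 0.05: m = 20; DE = 1 + 19 × 0.05 = 1.95; inflation = 2.95/2 = 1.475; 1.96/√1.475 = 1.614, giving 10.7%; SE = 0.8 × √(2.95/80) = 0.154; 2.80 × 0.154 = 0.43.

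**Step 3: simulation of the individual-level analysis of covariance** (4,000 replicates per setting).

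- Coach variance in the scheduled level only, ICC 0.05: with 4 coaches the true SE is 0.153 against a model SE of 0.126, and type I error is 0.10. With 8 coaches the figures are 0.142, 0.126 and 0.08.
- Same coaches with one common effect in both levels, 4 or 8 coaches, ICC 0.02 to 0.10: the true SE is 0.121 to 0.126 against a model SE of 0.125 to 0.127, and type I error is 0.041 to 0.047. Here the SE is not too small.

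**Step 4: small-sample degrees of freedom.** Step 2 uses a normal approximation, which flatters the plan when coaches are few. For 4 coaches and ICC 0.05, the two mean variances are 0.64 × 1.95/80 = 0.0156 (3 df) and 0.64/80 = 0.0080 (79 df). Satterthwaite df = 0.0236² / (0.0156²/3 + 0.0080²/79) ≈ 6.8, with a t value of about 2.38. Against the present 1.975, the interval is (2.38/1.975) × √1.475 ≈ 1.46 times as wide.

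**The case against.** A reader might infer that the standard error is too small as a matter of fact, and that 0.36 is therefore wrong. The documents do not support that. The result needs a coach ICC above zero and coach variation that differs between the two levels, and the article gives no ICC, coach number or assignment rule. Participants in all arms have an orientation call with a coach, and those without scheduled calls can still reach the coaching team, so coaches may serve both levels. A common effect would then largely cancel, as Step 3 shows.

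A reader might also infer that one coach delivers all 24 weekly calls. The article says only that there is a primary coach who schedules the first call; shared delivery would lower the ICC. Calls follow a common content outline, and delivery is audited with checklists, call logs and recordings. Both favour the low end of the ICC range.

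The type I figure also depends on the inference target. If calls changed nobody's outcome, coaches would add no level-specific variance and the error rate would stay at 5%. The inflation describes a zero average effect over a population of coaches who differ. Inference about this coaching team alone would be legitimate, but the Discussion draws lessons for future programs, which favours treating coaches as a sample.

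Finally, the trial calls itself exploratory, and the analysis plan, which is not shown, could add a coach term. That lowers the weight of the point without removing it: the article itself states which correlation is handled and prints a detectable difference that holds only under independence.

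**Conclusion.** The point holds in conditional form. The stated model and the 0.36 allow only for repeated measures within a participant, in a design that concentrates coach contact in one level of a tested factor. If coaches differ and that variation sits mainly in the scheduled-call level, the coaching effect will look more certain than it is. Under the assumed range in Step 2 (4 to 8 coaches, ICC 0.01 to 0.05) the consequence runs from negligible to a doubling of the nominal error rate, before any small-sample correction. At the favourable end, 0.36 stands.

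It would be wrong to extend this to the whole trial. The gamification main effect is largely unaffected if each coach serves both reward types. This is a cheap improvement to the coaching analysis, and it does not show that the plan is invalid.

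**What to change.** 1. Record each participant's primary coach and, where feasible, balance each coach's caseload over gamified and flat rewards.
2. Prespecify a sensitivity analysis of the coaching effect with a coach random effect confined to the scheduled-call level and small-sample degrees of freedom. It should act on the 6-month outcome, since coaches are met only after baseline and a constant coach intercept would drop out of the change. If coaches are too few for a stable variance estimate, report the coaching effect with standard errors inflated over ICC 0.01 to 0.05.
3. State in Sample Size that 0.36 assumes no coach clustering, and give a range for the coaching effect (0.36 to 0.43 under the assumptions above, to be redone with the actual number of coaches).

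The cost is some record keeping, attention to caseloads, one added analysis and a wording change. The price in results is a wider interval for the coaching effect and a less favourable detectable difference. With few coaches the widening is substantial: about 46% with 4 coaches and an ICC of 0.05.

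### Covariates are chosen by chance baseline imbalance plus corrected AIC: this contradicts the claim of prespecification and gives up some power, but does not inflate type I error

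*Protocol article*

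**What the plan says.** All of this is in the protocol article, mostly under Statistical Methods.

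- **Screening.** After randomisation, "key variables such as age, race, sex, disability type, and physical function at baseline will be examined and compared for relationships with study arms". The list is illustrative, not closed.
- **Selection.** A variable must pass two gates, imbalance and fit: "If a potential confounder is found to differ meaningfully among the groups and if we find that the inclusion of the covariate improves". Fit is judged by corrected AIC, and a variable that passes both gates joins the model. The size of a meaningful difference is not defined. Nor is it said whether a selected variable enters as a main effect or with a time interaction.
- **Prespecification.** The same section states: "The significance tests conducted for the primary outcome are all specified a priori and modest in number".
- **Tested effect.** The component effects are pre-post contrasts between baseline and 6 months: "these effects will be modeled as component-by-time interactions, with the 6-month outcome as the primary end point".
- **Sizing.** Sample Size rests on analysis of covariance with a baseline covariate. The calculations "assume an overall 2-sided type I error rate of 5%, 80% power".

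**The concern.** Allocation is computer-generated and happens only after the baseline survey is complete (Allocation; Randomization). Any baseline difference between arms is therefore chance, not confounding. What makes a covariate worth including is how well it predicts the outcome, and that is known or assumed before the data arrive. A gate on observed imbalance has three consequences:

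- The primary model depends on the realised allocation and, through the AIC step, on the outcome data. That does not fit with tests all fixed beforehand.
- A strong predictor that happens to be balanced is left out, and its precision gain is lost.
- With no threshold and an open list, two analysts could reach different primary models from the same data.

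A further question is whether a covariate that passes both gates would help the contrast being tested, since that contrast is a change over time.

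**Working it through.** **Inputs from the protocol article.** Sample Size: two-sided 5%, 80% power, baseline-outcome correlation r = 0.6, d = 0.36, and "We will assume an attrition rate of 20%, with 160 (80%) participants completing the study". Allocation: 1:1:1:1, hence 80 completers per factor level.

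**Assumed, not in the article.** The threshold for a meaningful difference, the number and independence of the candidates, and the share R² of residual variance they explain.

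**Step 1: reproduce the plan's figure.** For an ANCOVA main effect, d = (1.960 + 0.842) × √[(4/160)(1 − 0.6²)] = 2.802 × √0.016 = 0.354. The article states 0.36, so it reproduces. Power at 0.36 is 81%.

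**Step 2: how often chance alone opens the imbalance gate.** With the five named candidates treated as independent, the probability of at least one flag is 1 − 0.95⁵ = 23% at p < 0.05 and 1 − 0.90⁵ = 41% at p < 0.10. The form of the primary model therefore depends heavily on an unstated cut-off.

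**Step 3: power.** With fixed covariates, SE = √[(4/160) × 0.64 × (1 − R²)] and power ≈ Φ(0.36/SE − 1.96). At R² = 20%, SE = √0.0128 = 0.113, and 0.36/0.113 − 1.96 = 1.22, giving 88.9%. The simulated columns use ANCOVA, N = 160, r = 0.6 and a gate of standardised difference above 0.2 plus corrected AIC.

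| Assumed R² | Fixed, formula | Fixed, simulated | Rule, simulated | Gap (simulated) |
|---|---|---|---|---|
| 5% | 83.1% | 81.6% | 80.9% | 0.7 |
| 10% | 85.1% | 83.3% | 80.6% | 2.7 |
| 20% | 88.9% | 88.0% | 83.7% | 4.3 |
| 30% | 92.5% | 90.7% | 84.8% | 5.9 |

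The formula ignores the degrees of freedom spent, so it runs about 1 to 2 points high. Other runs with the same kind of gate gave gaps of 3.5 points (83.9% against 87.4%) and 4.9 points (82.3% against 87.2%) at R² = 20%. At R² = 2% there was no gain from fixed adjustment (80.5%, against 81.0% under the rule).

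**Step 4: type I error.** Under the rule it is near 5% at R² of 5% to 10%, 4.2% at 20% and 3.8% at 30%. Two other runs at 20% gave 4.0% and 4.6%. With a different assumed gate (arm comparison at p < 0.10, five candidates, 6,000 null trials per scenario) it was 4.9% to 5.1% with weak covariates and 3.7% to 3.8% with strong ones. Fixed adjustment gave 4.9% to 5.1%. For a rate near 5%, the simulation standard error at 6,000 trials is √(0.05 × 0.95/6000) = 0.28 points. The shortfall arises because the rule removes the larger chance imbalances but keeps the unadjusted, wider standard error when the covariate is balanced.

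**Step 5: what a main effect does to the planned contrast.** In a two-visit random-intercept model that keeps the factor main effects, complete data make the component-by-time estimate a difference in mean change, y(6 months) − y(baseline). A time-constant covariate entered as a main effect cancels from that difference. Fits at N = 160 agree: the largest difference was about 2 × 10⁻¹⁵ in the estimate and 2 × 10⁻⁶ in the standard error. With about 20% of 6-month scores missing (N = 200, 12 trials per scenario, covariate-outcome correlation 0.5 assumed):

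- the estimate moves by 0.012 to 0.015 SD on average and at most 0.035 SD, which is 0.035/0.12 = 0.29 of a standard error;
- a single p-value moved by as much as 0.22;
- the mean standard error falls from 0.1230 to 0.1224 (missing completely at random) or from 0.1227 to 0.1215 (missing at random), 1% or less.

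For scale, the change contrast at r = 0.6 has a detectable difference of 2.802 × √[(4/160) × 2(1 − 0.6)] = 0.396 and 72% power at 0.36, against 81% for the ANCOVA of Step 1. With complete data, covariate main effects cannot close that gap.

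**The case against.** The strongest reply has four parts.

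**The harm is modest and depends on assumptions.** This stands. At R² of 5% or less the loss is under 1 point, and at 10% it is 2 to 3 points. The rule is also not worse than no adjustment: in one run at R² = 20%, power was 80.2% unadjusted, 82.3% under the rule and 87.2% with fixed covariates. The loss is relative to a better method that uses data already collected.

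**The trial is exploratory and the statistician is blinded.** Statistical Methods calls the trial exploratory, and Blinding (Masking) keeps the primary statistician blind. Both limit deliberate steering and lower the stakes. Neither supplies a threshold, closes the list or recovers precision.

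**Details can be left to an analysis plan.** This holds for the form of entry, which is no fault in itself. It does not cover the selection rule, which the article states and commits to.

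**Stronger readings go too far.** A reader might infer that covariate adjustment does nothing for the primary test. The article does not say that covariates enter as main effects only, and the invariance is exact only with complete data, whereas 20% attrition is planned and incomplete cases stay in the mixed model. The power figures above were also computed under ANCOVA, so they do not measure loss in the component-by-time model. A reader might also infer that physical function at baseline is the SF-36E subscale and so already a response in the model. That is plausible, but not stated: Eligibility Criteria names a separate physical functioning screen from NHANES, and the subscale would in any case not be a response in the emotional well-being model.

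**Conclusion.** The point holds. The article commits to a data-driven covariate rule with no threshold and an open list, justified by imbalance that randomisation makes a matter of chance. This contradicts its own statement that the primary tests are all fixed in advance.

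The cost against fixed adjustment is about 1 to 6 points of power at d = 0.36 for an assumed R² of 5% to 30%, with ANCOVA, 160 completers, r = 0.6 and an assumed gate of a standardised difference above 0.2. The article gives neither the R² nor the gate.

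A reader might expect a data-dependent model to produce too many false positives. The calculations do not support that for mechanical use: the error rate is near 5%, or below it when covariates are strong. They do not cover discretionary use of the undefined threshold. Main-effect entry would add almost nothing to the planned contrast, but that is conditional on a form the article leaves open.

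**What to change.** - Delete the imbalance and corrected-AIC gates.
- Name a short set of prognostic covariates in advance from those already listed, for example age, sex and disability type, and include them in every primary model whatever the observed balance.
- State that they act on the 6-month score. One way is ANCOVA with the baseline outcome as a covariate, which matches Sample Size. The other is covariate-by-time terms in the mixed model; there the baseline outcome stays a response and is not also entered as a covariate.
- If physical function at baseline is kept, say which instrument it comes from.
- Keep the between-arm comparison of baseline variables descriptive.

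The cost is a change of wording and a few degrees of freedom, mainly for disability type. No new data are needed, since the candidate variables are already planned for examination at baseline.
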